### Sample size and power calculation

Comparable studies to guide a potential anticipated effect for power calculation are lacking. However, similar studies investigating the outcome of attention utilizing computerized gaming interventions report within-group improvement scaling from one to two standard deviations [51]. In addition, a cross-sectional study investigating a similar population at two time points with the same outcome measures was also utilized [52]. The sample size was calculated based on the coefficient of variation (CoV) of CPT as the primary outcome. A mean difference in change in CoV of CPT of 3% between baseline and follow up between the groups was defined as a clinically important difference. With equal allocation to both treatment groups and with an SD of 5%, power of 80%, and a significance level of 5%, the sample size was calculated to be 45 patients in each group. Allowing for 10% drop out, we aim to include a total of 100 patients.

The sample for qualitative interviews will be selected using selective sampling, meaning selecting individuals who are knowledgeable about the intervention or phenomenon being studied [53]. In this study, the sample will be the first ten participants that finish the VR intervention period.

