**Methods:**

One hundred participants (18–65 years), with a verified ABI, impairments of processing speed/attention, and/or working memory, and a minimum of 12 months post injury will be recruited. Participants with severe aphasia, apraxia, visual neglect, epilepsy, and severe mental illness will be excluded.

Participants will be randomized into two parallel groups: (1) an intervention group playing a commercial VR game taxing processing speed, working memory, and sustained attention; (2) an active control group receiving psychoeducation regarding compensatory strategies, and general cognitive training tasks such as crossword puzzles or sudoku. The intervention period is 5 weeks. The VR group will be asked to train at home for 30 min 5 days per week.

Each participant will be assessed at baseline with neuropsychological tests and questionnaires, after the end of the intervention (5 weeks), and 16 weeks after baseline. After the end of the intervention period, focus group interviews will be conducted with 10 of the participants in the intervention group, in order to investigate acceptance and tolerability of VR as a training method.

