A relatively recent review of VR interventions in cognitive rehabilitation after ABI identified only 13 studies [16]. While most of them concluded that VR was an effective method for training attention, memory, and problem-solving, scrutiny revealed severe methodological challenges. Only half of the studies involved immersive VR [23–28], while the rest used video games played on a screen. All studies utilizing immersive VR were published previous to the first generation of the VR systems that are in use today, rendering the technology non-comparable. Furthermore, small sample sizes were the norm and several studies were single case studies or lacked control groups [19]. Importantly, none investigated the effect of playing commercial VR games. There is thus a need for well-controlled randomized trials exploring the effectiveness of VR interventions in cognitive rehabilitation after ABI, and possible transfer effects to everyday activities [29].

Motivating effects of VR for healthy people are well established [30]. Our clinical experience, and the preliminary existing literature, indicates that most patients find it motivating to use VR for training purposes as well and tolerate it without major adverse effects. Cybersickness and fatigue are potential side effects of VR, particularly after extended use [31]. Cybersickness is similar to motion sickness, and it is not known if persons with ABI are more susceptible to these adverse effects, or if VR may exacerbate pre-existing symptoms in some individuals. To our knowledge, the only study reporting adverse effects of VR in an ABI population found that the technology was well tolerated by 18 of 21 patients [27], and that those who were not able to complete the training experienced “fatigue and frustration.” Furthermore, there are likely individual differences, both related to injury and other factors, when it comes to who might benefit from VR in rehabilitation. This has however not been systematically investigated.

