**Fig. 1 Fig1:**
[figure not shown]
Overview of study design

The primary and secondary outcome measures will be re-administered at the end of the 5-week intervention period (T2) and 16 weeks (T3) after baseline. After T3, the first ten participants from the VR group will be asked to take part in individual qualitative interviews to gain in-depth understanding of their experience with the use of VR as a training method and participation in the intervention.

The RCT will follow the CONSORT statement [35] and is registered in ClinicalTrials.gov (NCT05443542) and Open Science Framework (osf.io/6gphy). When preparing this protocol, we used the SPIRIT reporting guidelines and the SPIRIT checklist is available as an additional file (Additional file 1).

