Reviews call for further investigation of transferability of training effects after the use of VR into everyday functioning, larger and more homogenous sample sizes and utilizing proper control conditions [18, 29, 59]. To our knowledge, no studies have been performed with the methodological quality of the present study, and none has investigated whether the effects of VR training transfer into everyday functioning. This study will address all of these needs by including an adequate number of participants in reference to the sample size calculation, rigorous selection criteria and investigating everyday functioning both quantitatively and qualitatively.

There are many unknown factors with regard to the tolerability of VR use in the ABI population and persons with ABI. Thus, there is a need to investigate the acceptability and possible adverse events, i.e. tolerability, in more detail than previously evident in research performed on VR [19]. This study will qualitatively investigate the subjective experiences of using VR as a method of cognitive training in a subgroup of participants (*n* = 10). We will also explore the tolerability and acceptability of the intervention. Furthermore, all participants randomized to VR training will answer weekly questionnaires regarding adverse events, such as fatigue and cybersickness. Cybersickness is relatively rare while using VR, but it may be particularly relevant to assess in the ABI population as injuries to the brain may lead to symptoms that are comparable to symptoms of cybersickness. The qualitative data, in combination with the quantitative data collected during the intervention period, will provide valuable information regarding the usability, acceptability and tolerability of VR in the ABI population.

Many patients wish to continue cognitive training after being discharged from the hospital. If the present study shows VR to be effective, the intervention may provide an opportunity for persons with ABI to continue to do cognitive training after post-acute rehabilitation.

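### Interviews on acceptance and tolerability are limited to the first ten who finish VR, so early stoppers are not heard; the eligibility rule and the interview format also differ between sections

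*Protocol article*

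**What the plan says.** Three places in the protocol article describe the interview sample.

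- **Sample size and power calculation:** "the sample will be the first ten participants that finish the VR intervention period". The approach is called selective sampling, explained as "selecting individuals who are knowledgeable about the intervention or phenomenon being studied".
- **Study design (text after Fig. 1):** "After T3, the first ten participants from the VR group will be asked to take part in individual qualitative interviews". Finishing is not mentioned.
- **Abstract, Methods:** "focus group interviews will be conducted with 10 of the participants in the intervention group, in order to investigate acceptance and tolerability". Neither finishing nor order of entry is mentioned.

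Three other places show that the plan expects some intolerance. The Background cites one earlier study in acquired brain injury that "found that the technology was well tolerated by 18 of 21 patients", and reports fatigue and frustration in those who could not complete. Aims and hypotheses expects a minority with adverse effects. Randomization and allocation concealment states that allocation stays unchanged for participants who do not tolerate the intervention.

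**The concern.** Whether someone finishes five weeks of VR depends partly on how well they tolerate it. A sample restricted to finishers is therefore selected on the very thing the interviews are meant to describe. The Background makes this link itself: in the cited study, the people who could not complete were the ones reporting fatigue and frustration.

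At stake is the qualitative account of how VR is experienced, which serves a declared secondary aim. An account drawn only from finishers is likely to read more favourably than one drawn from all VR participants. It also has nothing to say about why people stop, although the interview guide covers topics such as perceived effort and belief in one's ability to take part, on which early stoppers would be informative.

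The stated rationale does not settle the matter. People who stopped because of symptoms also know the intervention, and taking the first ten finishers is consecutive sampling of completers, whatever name it is given.

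**Working it through.** **1. Eligibility and format, side by side**

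| Section | Who | Format | When |
|---|---|---|---|
| Abstract, Methods | 10 from the VR group | Focus group | After the intervention period |
| Study design | First ten from the VR group | Individual | After T3 |
| Sample size and power calculation | First ten who finish VR | Interviews, type not given | Not given |

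- *Eligibility:* Study design could admit an early stopper; Sample size and power calculation, read plainly, cannot. These are different rules.
- *Format:* focus group and individual interview are incompatible.
- *Timing:* T3 is week 16 and the intervention ends at week 5, so an interview after T3 is also after the intervention. The two statements are compatible.

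**2. The VR arm size**

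Inputs from Sample size and power calculation: difference 3, SD 5, power 80%, significance level 5% (taken as two-sided), 10% dropout.

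- Normal approximation: n = 2 × (1.96 + 0.84)² × 5² / 3² = 43.6, so 44 per group. The t-test version gives 44.6, so 45, as stated.
- With dropout: 45 / 0.90 = 50 per group, 100 in total, as stated.

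The trial's sample size reproduces, and this point does not affect it. The ten interviews are a fixed choice with no calculation behind them.

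**3. How many VR participants the finishing rule could leave out**

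The document gives no expected rate of stopping VR early. Two of its figures can stand in, both by assumption:

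- Earlier study: 21 − 18 = 3 not tolerating; 3/21 = 14.3%; 50 × 0.143 = 7.1, about 7.
- Planned dropout: 50 × 0.10 = 5.

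Over a wider assumed range of 5% to 20%, the number is 2.5 to 10 of 50. The exact 95% interval for 3/21 is 3.0% to 36.3%, or about 1.5 to 18 of 50, so the earlier study pins the rate down poorly.

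Whatever the rate, the number of early stoppers interviewed under the finishing rule is 0.

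**4. Whether dropping the finishing condition is enough**

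For ten consecutive VR participants taken regardless of completion, the chance of including no early stopper is (1 − p)¹⁰:

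- p = 14.3%: 0.21
- p = 10%: 0.35

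Removing the condition would therefore still miss early stoppers fairly often. This supports including some on purpose. It does not measure the bias.

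**The case against.** **Other tolerability data.** A reader might infer that the trial's whole answer on tolerability is biased. The document does not support that. Table 1 gives weekly cybersickness and fatigue questionnaires to the VR group, and the Discussion says that all randomised to VR will answer them. The weekly calls monitor adverse events and ask about adherence, the game records play time, and the Discussion plans to read the qualitative and quantitative data together. This stands and confines the point to the interviews. Two qualifications remain: weekly responses may be missing after someone stops, and symptom scores do not replace an account of why they stopped.

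**Meaning of finish.** The phrase could mean reaching week 5 regardless of use. Completion is the more natural reading, but the ambiguity is real, and Study design omits the condition altogether. The exclusion is therefore the plain reading of one section, not a rule stated consistently.

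**Purpose of the interviews.** The secondary aim concerns experience of VR, and the interview guide rests on an acceptability framework; fully exposed participants suit both. This narrows the point, but the Abstract names tolerability explicitly: "in order to investigate acceptance and tolerability of VR as a training method". Finishers with symptoms can still be interviewed, so adverse experience is under-represented, not absent.

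**Timing.** A reader might see a conflict between interviews after the intervention and interviews after T3. There is none, as shown in the working.

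**Magnitude.** It is tempting to express the bias as the chance that a random ten of 50 would include a non-tolerator: 81% if 7 of 50 do not tolerate VR, 69% if 5 of 50. The arithmetic is right, but it rests on an assumed rate, treats not tolerating as stopping early, and uses a random-sample comparator that the protocol does not propose. The Background itself calls the technology of the earlier immersive studies non-comparable with current systems.

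**Conclusion.** The point holds for the interview component. On its plain reading, the rule in Sample size and power calculation selects on completion, while the Abstract makes tolerability part of the purpose and the document expects some participants not to tolerate VR. Early stoppers contribute no interviews, so the interview findings under-represent intolerance and cannot explain stopping. The Limitations section does not mention this selection.

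Separately, the sections contradict each other on eligibility (finishing required or not) and on format (focus group or individual), and this needs reconciling whatever one thinks of the bias.

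The size of the bias cannot be computed from the document. If 10% to 14% stop early, about 5 to 7 of 50 VR participants would be outside the interview sample; this assumes that the planned dropout rate or the earlier study's non-tolerance rate carries over to stopping VR here. The primary outcome, its analysis and the sample size are untouched. Label: cheap improvement.

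**What to change.** 1. State one eligibility rule and one format in the Abstract, Study design, and Sample size and power calculation.
2. Draw the ten interviewees from everyone randomised to VR, and purposively include some who stopped early, had low play time or had high cybersickness scores. The play-time records and weekly questionnaires already planned can identify them.
3. Recruitment began in November 2022, so the ten interviews may already be done. In that case, either add a few early stoppers or state in the Limitations and in the report that the interviews describe completers only.

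**Cost:** if the interviews are not yet held, this is a change of wording with the same number of interviews. If they are, it means a few extra interviews or one sentence of limitation. Early stoppers may be harder to recruit, and the interview phase may end later.

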### Qualitative analyses

After all the interviews have been conducted, thematic analysis will be applied, following these six steps: (1) Organizing and preparing data, including transcribing and sorting field notes. (2) Reading through all the data, to obtain a general sense of what the information given by the participants. (3) Coding the data and organizing the material into segments of texts to start bring meaning to the information. (4) Separate the information into “descriptions” and “themes”. (5) Check for interrelating themes and descriptions. (6) Interpret the meaning of the themes and descriptions [54].

### Dissemination plan

The study plans for at least three publications in international peer-reviewed journals. We expect the novelty and innovative aspects of the study to allow for publication in high-impact journals within the field of neurology/rehabilitation and health innovation. Results will be disseminated in relevant expert forums, national meetings, conferences, and popular scientific journals and reports. Members of the local research group all have central positions within research, clinical management, and innovation at SRH. Implementation of study findings into clinical practice will thus be highly feasible. SRH plays a major role in spreading knowledge and contributing to the implementation of new knowledge throughout the rehabilitation sector, i.e., through hosting the South Eastern Regional Competency Centre for Rehabilitation. This will provide ample opportunity for national dissemination of results. The international collaborators will help to improve international dissemination of the results. We also expect study findings to be of interest for the general public.

## Discussion

The present RCT aims to investigate whether playing a VR game is an effective method of training processing speed, working memory, and sustained attention in persons with ABI. Furthermore, the study will explore if effects transfer to everyday functioning, and explore acceptability and tolerability of using VR for patients with ABI.

The research field regarding VR in cognitive rehabilitation is characterized by optimism, and a recent update to clinical guidelines of cognitive rehabilitation has listed VR as a method of cognitive training with level A for executive functions [55]. These recommendations are based on two reviews, including 9 and thirteen primary studies respectively [16, 56] and one cohort study [57]. However, closer scrutiny of the primary studies revealed that they have limitations. These limitations are in line with what Vlake and colleagues specify as common limitations in early VR studies: heterogeneous groups, lack of controls, and small samples [19]. In addition, the reviews pool together results from trials utilizing both immersive and non-immersive VR. A major shortcoming of available VR research today is that there are almost as many reviews as primary studies, which again may lead to an unqualified positive assessment of the existing evidence base. On this background, Vlake and colleagues call for large-scale studies with more homogenous groups and appropriate control conditions [19]. The present study thus represents a needed contribution to the field.

No studies have so far investigated the use of commercially available VR games in cognitive rehabilitation. However, BeatSaber has been suggested as an appropriate game to use in cognitive rehabilitation by Tao and colleagues [58]. Furthermore, based on clinical experience, our research team’s recognizes it as cognitively challenging, as it requires the player to react to stimuli with increasing speed and difficulty thus taxing both processing speed, sustained attention, and working memory.

Reviews call for further investigation of transferability of training effects after the use of VR into everyday functioning, larger and more homogenous sample sizes and utilizing proper control conditions [18, 29, 59]. To our knowledge, no studies have been performed with the methodological quality of the present study, and none has investigated whether the effects of VR training transfer into everyday functioning. This study will address all of these needs by including an adequate number of participants in reference to the sample size calculation, rigorous selection criteria and investigating everyday functioning both quantitatively and qualitatively.

There are many unknown factors with regard to the tolerability of VR use in the ABI population and persons with ABI. Thus, there is a need to investigate the acceptability and possible adverse events, i.e. tolerability, in more detail than previously evident in research performed on VR [19]. This study will qualitatively investigate the subjective experiences of using VR as a method of cognitive training in a subgroup of participants (*n* = 10). We will also explore the tolerability and acceptability of the intervention. Furthermore, all participants randomized to VR training will answer weekly questionnaires regarding adverse events, such as fatigue and cybersickness. Cybersickness is relatively rare while using VR, but it may be particularly relevant to assess in the ABI population as injuries to the brain may lead to symptoms that are comparable to symptoms of cybersickness. The qualitative data, in combination with the quantitative data collected during the intervention period, will provide valuable information regarding the usability, acceptability and tolerability of VR in the ABI population.

Many patients wish to continue cognitive training after being discharged from the hospital. If the present study shows VR to be effective, the intervention may provide an opportunity for persons with ABI to continue to do cognitive training after post-acute rehabilitation.

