### Aims and hypotheses

The primary aim of this study is:

To evaluate the effect of playing a commercial VR game as a means of re-training of processing speed, working memory, and sustained attention in persons in the chronic phase of acquired brain injury.

Secondary aims are to explore:Transfer effects to everyday functioning.How ABI patients experience using VR.How fatigue, motivation and presence is affected by VR training.

We hypothesize that the intervention group will demonstrate improved processing speed, working memory, and sustained attention compared to an active control group.

We furthermore hypothesize to find generalization of VR treatment effects to improved everyday functioning. Finally, we anticipate that the majority of patients with ABI will tolerate the use of VR well, and find the method motivating, but that a minority will experience adverse effects.

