### Descriptive and outcome measures

All outcome measures will be administered at T1, T2, and T3. The primary outcome is sustained attention and will be measured by the coefficient of variation (CoV) on the Conners Continuous Performance Test 3rd (CPT 3) [36]. Secondary outcomes are CPT 3, Mean hit Reaction time, Weschler Adult Intelligence Scale IV, Backwards Digit Span and Digit Sequencing [37], and patient competency rating scale [38]. Psychometric properties for each measure are acceptable. See Table 1 for an overview of all primary and secondary outcome measures, citations for psychometric properties, respondents, and time points.

**Table 1 Tab1:** Outcome measures, respondents and time points

*Outcome domain*	*Measure*	*Respondent*	*Time point*
**Sustained attention**	Conners Continuous Performance Test 3rd, coefficient of variation [39]	All participants	T1, T2, T3
**Processing speed**	Conners Continuous Performance Test 3rd, Mean hit Reaction time [39]	All participants	T1, T2, T3
**Working memory**	Weschler Adult Intelligence Scale IV, Backwards Digit Span and Digit Sequencing [40]	All participants	T1, T2, T3
**Everyday functioning**	Behavior Rated Inventory of Executive Functioning – Adult, working memory scale	All participants and next of kin	T1, T2, T3
	Patient Competency Rating Scale [38]	All participants	T1, T2, T3
**Motivation**	Situational Motivation Scale [41]	All participants	Weekly during intervention period
**Fatigue**	Fatigue severity scale [34]	All participants	Weekly during intervention period
**Cybersickness**	Simulator sickness questionnaire	Participants in VR group	Weekly during intervention period
**Sense of presence**	Multi-Modal Presence Scale [32]	Participants in VR group	Weekly during intervention period

At baseline (T1), neuropsychological test measures and questionnaires will be used for descriptive purposes. The following neuropsychological test battery will be applied: the Trail Making Test 4 (shifting) and subtest 3 of the Color Word Interference Test (inhibition) from the Delis-Kaplan Executive Function System test battery [42]. Abstract reasoning will be measured with Similarities and Matrices from WAIS IV [37]. Furthermore, we will include Coding from the WAIS IV as a measure of processing speed [37]. Immersive tendencies questionnaire will be administered at baseline to assess personality traits that may impact the level of experienced immersion [43].

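### As Table 1 schedules it, the simulator sickness questionnaire has neither a pre-VR score nor a control score, so its results cannot be attributed to VR or show worsening from a patient's own starting level

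*Protocol article*

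**What the plan says.** In the Protocol article, Table 1 (Descriptive and outcome measures) names the "Simulator sickness questionnaire" as the cybersickness measure. The respondents are "Participants in VR group" and the time points are "Weekly during intervention period". The Discussion agrees: "all participants randomized to VR training will answer weekly questionnaires regarding adverse events, such as fatigue and cybersickness".

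Two other places explain why the measure matters. The Discussion justifies it because "injuries to the brain may lead to symptoms that are comparable to symptoms of cybersickness". The Background notes that it is not known "if VR may exacerbate pre-existing symptoms in some individuals". The hypothesis in Aims and hypotheses is that "we anticipate that the majority of patients with ABI will tolerate the use of VR well", with adverse effects expected in a minority.

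The text above Table 1 also states: "All outcome measures will be administered at T1, T2, and T3". This does not match the table's rows for the weekly measures. Fig. 2, the SPIRIT schedule, is not available in the text reviewed.

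**The concern.** The protocol gives its own reason to expect a non-zero score without VR: the injury may produce similar symptoms. A score first taken after exposure has begun, in the exposed arm only, mixes existing symptoms with any effect of VR. Worsening is a change from an earlier level, and Table 1 lists no earlier level.

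At stake is the interpretation of the one instrument aimed at cybersickness. If scores are high, the trial cannot say whether VR or the injury produced them. If some patients truly become worse, that cannot be shown against where they started. The Discussion presents tolerability as something this trial will examine in more detail than earlier work, and the Limitations section does not mention this restriction.

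**Working it through.** **1. The plan's own figures.** The protocol states no rate, cut-off or sample size for cybersickness. Its only sample size concerns the primary outcome: a difference of 3, SD 5, 80% power and 5% significance (taken as two-sided).
- Normal approximation: n = 2 × (1.96 + 0.84)² × 5² / 3² = 43.6, so 44 per group. The t-test version gives 44.6, so 45, as stated.
- Dropout: 90 / 0.90 = 100, as stated. With 1:1 allocation this is 50 per arm.

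These figures reproduce and enter below only through the 50 per arm.

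**2. Does the general T1/T2/T3 sentence supply a baseline?** Study design and Randomization and allocation concealment both place randomisation after the baseline assessment. At T1 there is therefore no VR group to which a questionnaire restricted to that group could be given. The sentence conflicts with the table row but does not establish a pre-VR score.

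**3. Do the other data fill the gap?**
- Fatigue is collected weekly in both arms, but it is a different construct, and Table 1 lists no T1 fatigue score either.
- Weekly calls in both arms monitor adverse events. Study design and Limitations describe their questions as specific to the allocated condition, so like-for-like symptom questioning is not established.
- Playing time is logged, but it is recorded as adherence and will also reflect motivation and technical problems.
- Interviews go to the first ten participants who finish the VR period (Sample size and power calculation), so those who stop because of symptoms are likely to be missed.

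These sources inform tolerability in general. None gives a before-and-after or between-arm comparison of cybersickness symptoms.

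**4. What the missing comparator costs (illustration; all rates assumed).** Let p be the proportion of the VR arm reporting symptoms by some chosen definition, and b the proportion who would do so without VR. The excess due to VR is p − b. Take p = 20/50 = 40% (exact 95% CI 26% to 55%).

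With VR-arm data only, b is unknown. Over b from 0% to 40%, p − b runs from 40 down to 0 points. A larger VR arm would narrow the interval for p but not this range.

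With the questionnaire also given to 50 controls, b is estimated, and the 95% CI is (p − b) ± 1.96 × √[p(1 − p)/50 + b(1 − b)/50]:

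| Assumed b | Excess | Standard error | 95% CI |
|---|---|---|---|
| 10% | +30 points | √(0.0048 + 0.0018) = 0.081 | 14 to 46 |
| 20% | +20 points | √(0.0048 + 0.0032) = 0.089 | 2 to 38 |
| 30% | +10 points | √(0.0048 + 0.0042) = 0.095 | −9 to 29 |

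**5. What remains estimable as planned.** The crude VR-arm rate can be estimated; for example, 10/50 = 20% has an exact 95% CI of 10% to 34%. Background symptoms would normally raise this rate, so a low value would be reassuring without a comparator.

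**The case against.** A reader might infer that the tolerability hypothesis cannot be answered at all. The documents do not support that. The hypothesis is largely descriptive and within the VR arm; it states no contrast with controls and no change from baseline. Playing time, adverse-event calls, interviews and a low crude symptom rate all bear on whether most patients tolerate VR. Background symptoms would also work against the hypothesis rather than flatter it. This objection stands and limits the point to attribution and worsening.

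A reader might also infer that every chronic symptom in the VR arm will be counted as cybersickness, and set an assumed count against the 3 of 21 patients in the earlier study cited in the Background. Neither step holds. The protocol sets no cut-off or label for cybersickness, and the 3 of 21 are patients who did not tolerate the technology, not a symptom prevalence.

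The protocol's wording is also cautious. It says that injury may lead to comparable symptoms, not that it causes the same ones. Worsening of existing symptoms is named as an unknown in the Background, not listed as an aim. The trial calls itself exploratory. All this lowers the weight of the point. It does not remove the gap, because the protocol itself raises the overlap and then schedules the measure so that the overlap cannot be resolved.

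Finally, with recruitment open since November 2022 and expected to end around April 2024 (Trial status), a change may reach only some participants. That is correct, and the fix allows for it.

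**Conclusion.** The point holds in a limited form. As listed in Table 1, the questionnaire can describe how often VR participants report symptoms during training. It cannot say how much of this is due to VR, or whether a patient became worse than before. In the illustration, the part due to VR is undetermined between 0 and 40 points. That range rests on an assumed 40% observed rate and an assumed background of 0% to 40%, since the protocol gives neither.

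The conclusion takes the Table 1 row as governing over the general timing sentence. If the unseen schedule in Fig. 2 places the questionnaire at T1 for all participants, the missing-baseline part falls and only the missing control scores remain.

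This is a secondary tolerability matter. The primary outcome, its sample size and the efficacy analysis are unaffected.

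**What to change.** - Give the questionnaire to all participants at T1, before randomisation and before any VR tutorial, and report change from T1. This alone meets most of the concern.
- Preferably, also add it to the weekly motivation and fatigue questionnaires that controls already complete, and report the between-arm difference with its 95% CI.
- Reconcile the Table 1 row with the sentence that places all outcome measures at T1, T2 and T3.
- For participants enrolled without these scores, report crude VR-arm symptom rates and state, in Limitations and in the results, that they cannot be attributed to VR.

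The cost is an amendment, a small added questionnaire burden (mainly for controls), and incomplete baseline data for those enrolled before the change. The restriction on interpretation costs nothing and applies even if no amendment is made.
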